### PEEP setting protocols

#### Control group

The EXPRESS protocol is as follows [10]: *V*_T_ = 6 mL/kg; inspiratory flow set at 60 l/min and end-inspiratory pause of 0.2-0.5 sec, PEEP set so that *P*_PLAT_, measured during the end-inspiratory pause of 1–3 s, will be within the following limits: 28 cmH_2_O ≤ *P*_PLAT_ ≤ 30 cmH_2_O;. FiO_2_ set to achieve a SpO_2_ > 88–95%.

In case of hypercapnia with pH < 7.30 despite a respiratory rate = 30–35, an increase in *V*_T_ up to 8 ml/kg will be allowed.

#### Intervention group

Full details of the procedures performed in the intervention group are provided in Fig. 2.

**Fig. 2 Fig2:**
[figure not shown]
Graphical representation of study procedures before randomization and after randomization in the IPERPEEP arm

*V*_T_ = 6 mL/kg; inspiratory flow set at 60 l/min resulting in an end-inspiratory pause of 0.2–0.5 s. Respiratory rate set between 20 and 35 to maintain pH > 7.30. FiO_2_ set to achieve a SpO_2_ > 88–95%.

In case of hypercapnia with pH < 7.30 despite a respiratory rate = 30–35, an increase in VT up to 8 ml/kg will be allowed.

PEEP will be ≥ 5 cmH_2_O and set to ensure the maximum recruitment observed in the PEEP trial, with a maximum permitted *P*_PLAT_ of 30 cmH_2_O.

In particular, when interpreting the results of the PEEP trial, RI across two adjacent PEEP levels will drive PEEP setting.
RI ≥ 1.5 between two PEEP levels will lead to the setting of the higher PEEP.RI < 0.5 will lead to the setting of the lower PEEP value.In case of RI ≥ 0.5 and < 1.5, the choice among two adjacent PEEP levels will be left to the attending physician, who will indicate the set PEEP in order to best balance between the commitment of limiting total, static, and dynamic strain and of optimizing oxygenation and hemodynamics.

Due to possible interferences with EELV measurement, in patients showing airway closure [31, 32, 34], no PEEP lower than the airway opening pressure will be tested or used in the IPERPEEP group for the whole duration of the intervention.

A similar 5-step PEEP trial will re-assess lung response to different levels of PEEP every 12–24 h, in case of changes in the body position or any other clinical events requiring modifications of the ventilatory settings.

Following PEEP trials will be conducted to investigate RI at the five PEEP levels closest to the set one.

Before the procedure, PEEP will be set for 15 min at the maximum PEEP expected to be tested during the PEEP trial, to ensure that *P*_PLAT_ remains below the safety limit with this setting: no PEEP< 5 cmH2O, generating *P*_PLAT_ > 30 cmH_2_O or lower than the airway opening pressure (in case of airway closure) will be tested or used over the entire course of the study in this intervention group. In particular, each following PEEP trial will investigate response to PEEP at values ranging from + 6 and − 6 than the previously set one (i.e., in case of previously set PEEP = 12, PEEP trial at 6-9-12-15-18; in case of previously set PEEP = 16, PEEP trial at PEEP = 10-13-16-19-22; in case of previously set PEEP = 8, PEEP trial at PEEP = 5-8-11-14).

The PEEP level will be then modified according to the strategy described above.

In both groups, the assigned ventilation protocol will be followed for a minimum of 72 h from randomization and any time fully controlled ventilation is deemed necessary by the attending physician up to 14 days from randomization. After 14 days from randomization, PEEP will be set according to the clinical practice of each institution.

### Measurements

All patients intubated due to hypoxemic respiratory failure and not included will be recorded on a dedicated screening log.

Demographics will be collected at study entry. Physiological variables will be recorded at the moment of enrolment (PEEP 5), after maximum PEEP is set before the PEEP trial, 1-6-12-24-48 h after randomization, and then on a daily basis up to 60 days or ICU discharge.

Data of the ventilation management (type of ventilation, FiO_2_, tidal volume, mean airway pressure, PEEP, plateau pressure, minute ventilation, respiratory rate, esophageal end-inspiratory and end-expiratory pressures, static stress, dynamic stress and total stress, proportion of spontaneous ventilation on minute ventilation, VO_2_, VCO_2_), physiologic data (heart rate, arterial pressure, SpO_2_, end-tidal CO_2_), and results of the blood gas analyses (pH, SaO_2_, PaO_2_, PaCO_2_, SvO_2_, PvCO_2_, oxygenation index, dead space fraction) will be collected.

*Respiratory mechanics* will be recorded at the moment of enrolment (PEEP 5), at each step of the first PEEP trial, and 1-6-12-24-48 h from randomization and then on a daily basis (72-96-120…) up to 60 days or ICU discharge. End-expiratory airway pressure (PEEP_AW_) and the end-expiratory esophageal pressure (PEEP_ES_) will be recorded during a 4-s expiratory hold. End-inspiratory airway pressure (*P*plat_AW_) and end-inspiratory esophageal pressure (*P*plat_ES_) will be measured during a 1-s end inspiratory hold. Expired tidal volume (*V*_T_) will be measured as the integration of the flow-time curve during expiration.

End-expiratory airway pressure (PEEP_AW_) and the end-expiratory esophageal pressure (PEEP_ES_) will be recorded during a 4-s expiratory hold. End-inspiratory airway pressure (*P*plat_AW_) and end-inspiratory esophageal pressure (*P*plat_ES_) will be measured during a 1-s end inspiratory hold. Expired tidal volume (*V*_T_) will be measured as the integration of the flow-time curve during expiration.

Advanced respiratory mechanics parameters will be computed afterwards. Stress will be calculated any time respiratory mechanics is measured, while strain will be measured before randomization in all patients and in the intervention group any time a PEEP trial is repeated; formulas are also shown in Table 1.

**Table 1 Tab1:** Computed respiratory mechanics parameters

*Parameter*	*Formula*
Airway driving pressure	ΔP = *P*plat_aw_ − PEEP_aw_
Transpulmonary end-inspiratory pressure	*P*plat_L_ = Plat_aw_ − *P*plat_es_
Transpulmonary end-expiratory pressure	PEEP_L_ = PEEP_aw_ − PEEP_es_
Lung driving pressure	ΔP_L_ = *P*plat_L_ − PEEP_L_
Lung plateau pressure, elastance-derived	*P*plat_L,EL_ = *P*plat_aw_ × (ΔP_L_/ΔP)
Static respiratory system compliance	Cst_RS_ = *V*_T_/ΔP
Static lung compliance	Cst_L_ = *V*_T_/ΔP_L_
Static chest wall compliance	Cst_CW_ = *V*_T_/(*P*plat_es_ − PEEP_es_)
Oxygenation-stretch index	OSI = PaO_2_/(FiO_2_ × ΔP)
Dynamic strain	Dynamic strain = *V*_T_/FRC_PEEPset_
Static strain (strain due to PEEP)	Static strain = (PEEP_volume_ − Rec_ZEEP-PEEP_)/FRC_PEEPset_
Static stress (stress due to PEEP)	Static stress = PEEP_aw_ × (ΔP_L_/ΔP)
Dynamic stress	Dynamic stress = *P*plat_aw_ × (ΔP_L_/ΔP)

The levels of *proinflammatory cytokines* (tumor necrosis factor [TNF], interleukin 6 [IL-6], and interleukin 8 [IL-8]) will be assessed from serum probes (enzyme-linked immunosorbent assay (ELISA)) of all included patients at study inclusion and 24, 48, and 72 h after randomization.

The following *scoring systems* will be calculated daily: simplified organ failure assessment score (SOFA), modified clinical pulmonary infection score (CPIS), and Richmond agitation and sedation scale (RASS). These systems and organ failure definitions used for the study purposes are reported in Additional file 2.

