### Study endpoints

The primary endpoint will be a composite clinical outcome that incorporates in-ICU mortality, 60-day ventilation-free days (VFD60), and the area under the curve of the interleukin-6 serum blood cytokine concentration (IL6AUC) during the first 72 h of observation.

Secondary endpoints will be as follows: ICU-, 90-day and in hospital mortality, 28 and 60-day ventilation-free days (VFD60), the area under the curve (AUC) of serum blood cytokines concentrations measured as stated in the study protocol; lung static, dynamic and total stress and strain after randomization; airway and lung driving and plateau pressures, compliance, compliance/PBW, dead space fraction, PaO_2_/FiO_2_ ratio, oxygenation stretch index and oxygenation index during the study treatment; and SOFA, CPIS, the incidence of complications or adverse reactions, the frequency and duration of other adjunctive therapeutic measures, transfusion requirements, the daily cumulative doses of analgesic and sedative agents, cumulative catecholamine requirements/24 h throughout the study period, frequency and duration of renal replacement therapy, the number of failing organs, and the “organ-failure-free days” within 28 days after randomization.

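### Table 1 gives dynamic stress the formula of elastance-derived lung plateau pressure, so this exploratory secondary endpoint contains the PEEP component and differs between arms wherever PEEP differs

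*Protocol article*

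**What the plan says.** All formulas are in Table 1 (section Measurements) of the protocol article.

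- Airway driving pressure: "ΔP = *P*plat_aw_ − PEEP_aw".
- Lung driving pressure: "ΔP_L_ = *P*plat_L_ − PEEP_L".
- Lung plateau pressure, elastance-derived: "P*plat_L,EL_ = *P*plat_aw_ × (ΔP_L_/ΔP").
- Static stress, labelled "Static stress (stress due to PEEP"): "Static stress = PEEP_aw_ × (ΔP_L_/ΔP").
- Dynamic stress: "Dynamic stress = *P*plat_aw_ × (ΔP_L_/ΔP").
- Dynamic strain, the parallel quantity on the volume side: "Dynamic strain = *V*_T_/FRC_PEEPset".

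The table has no row for total stress. The section Study endpoints names "lung static, dynamic and total stress and strain after randomization" among the secondary endpoints, and the Measurements section also lists static, dynamic and total stress as three separate items. The article gives no other formula for dynamic stress.

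**The concern.** Two differently named quantities share one formula. One of them, the elastance-derived plateau, is an end-inspiratory value that includes the effect of PEEP. The other, dynamic stress, stands beside a static stress row that is expressly the PEEP part, so it should hold the remaining tidal part. The strain rows make that split: tidal volume alone is the numerator of dynamic strain, and the PEEP volume appears only in static strain.

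This matters because PEEP setting is what the trial varies. The control arm holds plateau pressure at 28–30 cmH2O, whereas the intervention arm has a ceiling of 30 cmH2O and no matching floor. An endpoint proportional to plateau pressure will tend to be lower in whichever arm has less PEEP, and a reader would take this as less tidal stress. In addition, the Measurements section has stress calculated whenever mechanics are measured, in all patients. Strain after randomization is obtained only at repeated PEEP trials in the intervention group. Stress is therefore the static/dynamic split that can be compared between arms after randomization.

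**Working it through.** **Inputs from Table 1.** Write r = ΔP_L/ΔP, with Pplat and PEEP as airway values.

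- ΔP = Pplat − PEEP, so Pplat = PEEP + ΔP.
- Static stress = PEEP × r.
- Printed dynamic stress = Pplat × r.
- Elastance-derived lung plateau = Pplat × r.

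**Algebra.**

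Printed dynamic stress = (PEEP + ΔP) × r = PEEP × r + ΔP × r = static stress + ΔP_L.

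This is an identity and needs no assumption about patients. The printed value exceeds the tidal component by exactly the static stress. A numerical check on 10,000 random pressure sets agreed to rounding error (about 1e-14).

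If ΔP and r are equal in two patients, their printed values differ by (PEEP₁ − PEEP₂) × r, while ΔP_L does not differ at all.

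**Illustration.** The article gives no expected pressures by arm. All values here are assumptions, except that a plateau of 29 lies in the control arm's 28–30 band. ΔP = 12 and r = 0.75 in both arms.

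| | Control | Intervention | Difference |
|---|---|---|---|
| PEEP | 17 | 10 | 7 |
| Pplat = PEEP + 12 | 29 | 22 | 7 |
| Static stress = PEEP × 0.75 | 12.75 | 7.5 | 5.25 |
| Printed dynamic stress = Pplat × 0.75 | 21.75 | 16.5 | 5.25 |
| ΔP_L = 12 × 0.75 | 9.0 | 9.0 | 0 |

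The whole 5.25 cmH2O difference in printed dynamic stress is the difference in static stress.

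**Range.** Assume r 0.6–0.9, ΔP 10–14, control Pplat 29 (so control PEEP = 29 − ΔP, that is 15–19) and intervention PEEP 8–12, with ΔP and r equal between arms.

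- Smallest gap: (15 − 12) × 0.6 = 1.8 cmH2O.
- Largest gap: (19 − 8) × 0.9 = 9.9 cmH2O.

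**Direction can reverse.** Keep r = 0.75 and the control patient above, but give the lower-PEEP patient ΔP 14, so PEEP 10 and Pplat 24. The printed values are 18.0 against 21.75, which favours the lower PEEP. The tidal component is 14 × 0.75 = 10.5 against 9.0, which points the other way.

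**After correction.** Dynamic stress = (Pplat − PEEP) × r = ΔP × r = ΔP_L. Static + dynamic = PEEP × r + ΔP × r = Pplat × r, which is the elastance-derived plateau row. The three named stresses then fit together.

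**The case against.** The strongest reply concerns weight, because the algebra is not in dispute.

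- **Standing of the endpoint.** Stress is one item in a long secondary list, and the Statistics section treats all secondary analyses as exploratory. The primary composite (ICU mortality, VFD60, IL6AUC), the stratification and the stated sample size do not use it. The attending physician's choice of PEEP at intermediate recruitment-to-inflation ratios refers to strain, not stress. This stands.
- **The right quantity is already there.** Corrected dynamic stress is ΔP_L, and lung driving pressure is itself a listed secondary endpoint. In the illustration it would be reported as 9.0 in both arms and would contradict a spurious dynamic-stress result. This stands and lowers the severity, but it leaves a mislabelled endpoint in the same report.
- **Nothing is lost.** The underlying pressures are recorded, and derived parameters are to be calculated later. This stands.
- **The arms differ in the rule for PEEP, not necessarily in PEEP for each patient.** A highly recruitable intervention patient may end close to the control setting. This stands: the average artefact is unknown and may be smaller than the illustration. Holding ΔP fixed across PEEP levels is also a simplification.
- **The cause is unknown.** The row may be a misprint of ΔP as Pplat, or a total-stress formula under the wrong label. Either way, a named endpoint lacks a correct definition in this article.

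A reader might also infer that total stress is overstated because PEEP is counted twice. In the illustration, static plus printed dynamic stress in the control patient is 12.75 + 21.75 = 34.5 cmH2O, above the airway plateau of 29. The article does not support stating this as fact: it has no total-stress row and nowhere says that total is the sum of the two. If total stress is taken as the elastance-derived plateau, it is not overstated.

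**Conclusion.** The definition is wrong as written. Printed dynamic stress is identical to elastance-derived lung plateau pressure and exceeds the tidal component by the full static stress. That part follows from Table 1 alone. The size of the resulting between-arm gap rests on assumed pressures: 5.25 cmH2O in the illustration, and 1.8 to 9.9 cmH2O over the range tried, with equal ΔP and equal ΔP_L/ΔP in both arms. It vanishes where PEEP does not differ.

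It should be fixed, but it does not threaten the trial's main conclusion. It affects one exploratory secondary endpoint, can be recomputed from recorded data, and has its correct counterpart elsewhere in the endpoint list. Whether the analysis programs repeat the printed formula cannot be known from this article.

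**What to change.** In Table 1, change the dynamic stress row to (Pplat_aw − PEEP_aw) × (ΔP_L/ΔP), and note that this equals ΔP_L. Add a row for total stress, Pplat_aw × (ΔP_L/ΔP), stated as static plus dynamic stress and as equal to the elastance-derived lung plateau pressure. Check that the analysis programs follow these definitions, and note in the report that dynamic stress and lung driving pressure are then the same number, so they are not read as two independent results.

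The cost is one changed row and one added row. No new measurement is needed and no ventilator setting is touched. The article says enrolment had not begun, so the correction can precede any data.

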### Concomitant patient medical management

Concomitant patients’ management, including medical treatments and procedures, is detailed in Additional file 3.

### Study endpoints

The primary endpoint will be a composite clinical outcome that incorporates in-ICU mortality, 60-day ventilation-free days (VFD60), and the area under the curve of the interleukin-6 serum blood cytokine concentration (IL6AUC) during the first 72 h of observation.

Secondary endpoints will be as follows: ICU-, 90-day and in hospital mortality, 28 and 60-day ventilation-free days (VFD60), the area under the curve (AUC) of serum blood cytokines concentrations measured as stated in the study protocol; lung static, dynamic and total stress and strain after randomization; airway and lung driving and plateau pressures, compliance, compliance/PBW, dead space fraction, PaO_2_/FiO_2_ ratio, oxygenation stretch index and oxygenation index during the study treatment; and SOFA, CPIS, the incidence of complications or adverse reactions, the frequency and duration of other adjunctive therapeutic measures, transfusion requirements, the daily cumulative doses of analgesic and sedative agents, cumulative catecholamine requirements/24 h throughout the study period, frequency and duration of renal replacement therapy, the number of failing organs, and the “organ-failure-free days” within 28 days after randomization.

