**Methods:**

IPERPEEP is an open-label, multicenter, randomized trial that will be conducted in 10 intensive care units in Italy and will enroll 132 ARDS patients showing PaO_2_/FiO_2_ ratio ≤ 150 mmHg within 24 h from endotracheal intubation while on mechanical ventilation with PEEP 5 cmH_2_O.

To standardize lung volumes at study initiation, all patients will undergo mechanical ventilation with tidal volume of 6 ml/kg of predicted body weight and PEEP set to obtain a plateau pressure within 28 and 30 cmH_2_O for 30 min (EXPRESS PEEP).

Afterwards, a 5-step decremental PEEP trial will be conducted (EXPRESS PEEP to PEEP 5 cmH_2_O), and EELV will be measured at each step. Recruitment-to-inflation ratio will be calculated for each PEEP range from EELV difference. Patients will be then randomized to receive mechanical ventilation with PEEP set according to the optimal recruitment observed in the PEEP trial (IPERPEEP arm) trial or to achieve a plateau pressure of 28–30 cmH_2_O (control arm, EXPRESS strategy). In both groups, tidal volume size, use of prone positioning and neuromuscular blocking agents, and weaning from PEEP and from mechanical ventilation will be standardized.

The primary endpoint of the study is a composite clinical outcome incorporating in-ICU mortality, 60-day ventilator-free days, and serum interleukin-6 concentration over the course of the initial 72 h of treatment.

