### Statistics

All collected data will be tabulated descriptively by study group and analyzed on an intention-to-treat basis. Comparisons between groups will be performed with the chi-squared test or the Fisher’s exact test, as appropriate. Ordinal qualitative variables or non-normal quantitative variables will be compared with the Wilcoxon sum of ranks test. Quantitative normal variables will be compared with the Student *t*-test. In particular, analysis of the primary efficacy criterion will be performed with Wilcoxon-Mann-Whitney sum of ranks test.

Consistently to other published studies [22], every participant in the treatment group will be compared with every participant in the control group and assigned a score resulting from each comparison.

Mortality takes precedence over VFD60, which takes precedence over IL6AUC. Two VFD60s will be considered different for the purpose of scoring only if their difference is larger than 5 days. Similarly, two IL6AUC’s measurements will be considered different only if their difference exceeds 10% of the smaller of the two.

These individual-comparison scores are added up to obtain the cumulative score primary endpoint for each participant. Scoring system for the primary endpoint is detailed in Additional file 4.

For the purpose of the study, mechanical ventilation will be defined as: invasive mechanical ventilation with endotracheal tube or tracheostomy and noninvasive positive pressure ventilation, including continuous positive airway pressure. High flow oxygen therapy through nasal cannula or tracheostomy will not be considered as mechanical ventilation.

The assumptions and methodology used for the determination of the sample size are detailed in Additional file 5 [35]. Given the results obtained, and adopting a conservative approach in order to compensate for the small residual random variation in the numerical assessment of the sample size, it appears that a sample size of 56 subjects per arm would be sufficient to obtain 80% power in detecting a difference in the composite endpoint, at a type 1 error level of 0.05, two-tail. With an attrition rate of 15%, a total of 132 patients in two equal groups of 66 patients each should be enrolled. This corresponds to a mean of 19 patients per center.

Primary and secondary endpoints will also be analyzed in subgroups, as defined below:

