## Abbreviations

ARDS: Acute respiratory distress syndrome
AOP: Airway opening pressure
BMI: Body mass index
CNS: Central nervous system
COPD: Chronic obstructive pulmonary disease
CRF: Case report form
CPIS: Modified clinical pulmonary infection score
Cst_L\_: Static lung compliance
Cst_RS_: Static respiratory system compliance
Crec: Compliance of the recruited lung
CT scan: Computed tomography scan
ECCO_2_-R: Extracorporeal CO_2_ removal
ECMO: Extracorporeal membrane oxygenation
EELV: End-expiratory lung volume
EELV_REC_: Recruited volume
ELISA: Enzyme-linked immunosorbent assay
FiO_2_: Fraction of inspired oxygen
FRC: Functional residual capacity
FRC_PEEPset_: Aerated volume at set PEEP
GE Healthcare: General Electric Healthcare
ICU: Intensive care unit
ICUdeath: Mortality in ICU
IL: Interleukin
IL6AUC: Area under the curve of the interleukin-6 serum blood cytokine concentration
NIV: Noninvasive ventilation
NMBA: Neuromuscular blockade
NYHA: New York Heart Association
PBW: Predicted body weight
PaO_2_: Arterial oxygen partial pressure
PEEP: Positive end-expiratory pressure
PEEP_AW_: End-expiratory airway pressure
PEEP_ES_: End-expiratory esophageal pressure
PEEP_L_: End-expiratory transpulmonary pressure
PEEP_ES,ZEEP_: End-expiratory esophageal pressure
*P*plat_AW_: End-inspiratory airway pressure
*P*plat_ES_: End-inspiratory esophageal pressure
*P*plat_ESO_: End-inspiratory esophageal pressure
*P*plat_L,EL_: End-inspiratory elastance-derived transpulmonary pressure
*P*plat_L_: Transpulmonary pressure
RASS: Richmond Agitation and Sedation Scale
Rec_ZEEP-PEEP_: Recruited volume from ZEEP to PEEP
R/I: Recruitment-to-inflation ratio
SAPSII: Simplified Acute Physiology Score
SBT: Spontaneous breathing trial
SOFA: Sequential Organ Failure Assessment
SpO_2_: Oxygen peripheral saturation
TNF: Tumor necrosis factor
*P*_PLAT_: Plateau pressure
VFD60: 60-day ventilation-free days
VILI: Ventilator-induced lung injury
*V*_T_: Tidal volume

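### The top tier of the primary endpoint is death in the ICU, with no day limit stated, above a 60-day tier, so a patient who dies after ICU discharge outranks every ICU death

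*Protocol article*

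**What the plan says.** Study endpoints defines the primary endpoint as a "composite clinical outcome that incorporates in-ICU mortality, 60-day ventilation-free days (VFD60), and the area under the curve" of serum IL-6 over the first 72 hours. The Methods paragraph of the abstract agrees: "composite clinical outcome incorporating in-ICU mortality, 60-day ventilator-free days, and serum interleukin-6 concentration". Neither place attaches a day to the mortality component, and the Abbreviations list carries "ICUdeath: Mortality in ICU".

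Statistics fixes the order of the tiers: "Mortality takes precedence over VFD60, which takes precedence over IL6AUC". For the second tier it adds: "Two VFD60s will be considered different for the purpose of scoring only if their difference is larger than 5 days". The rest is referred elsewhere: "Scoring system for the primary endpoint is detailed in Additional file 4". That file is not available here.

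Deaths beyond the ICU appear only among the secondary endpoints ("ICU-, 90-day and in hospital mortality"), and Statistics treats all secondary analyses as exploratory.

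**The concern.** In a hierarchical comparison the first tier overrides everything below it. Here that tier is defined by where the patient dies, while the tier below it is defined by a fixed day.

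Two consequences follow from the wording. A patient discharged from the ICU on day 20 who dies on the ward on day 25 is not a tier-1 death, and so wins against every patient who died in the ICU. A patient who dies in the ICU on day 75 is, as worded, a tier-1 death, although the second tier closed at day 60.

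ICU discharge is decided by a team that knows the allocation. Death by a fixed day does not depend on that decision; death in the ICU partly does. At stake is whether the deciding component measures survival or a mixture of survival and discharge timing.

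**Working it through.** **Plan's own figure.** Inflating 56 per arm for 15% attrition gives 56/(1 − 0.15) = 65.9, so 66 per arm and 132 in total, as stated. This does not bear on the point. The assumptions behind the 56 are in Additional file 5 (not shown), so the power statement cannot be rebuilt. The article gives no death rates; all rates below are assumptions.

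**How many comparisons are touched.** Let q be the proportion dying after ICU discharge and by day 60, equal in both arms, and m the proportion dying in the ICU. The share of between-arm pairs with exactly one post-ICU death is 2q(1 − q):
- q = 2%: 2 × 0.02 × 0.98 = 3.9% of pairs (about 3 of 132 patients)
- q = 5%: 2 × 0.05 × 0.95 = 9.5% (about 7 patients)
- q = 10%: 2 × 0.10 × 0.90 = 18% (about 13 patients)

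At m = 35% and q = 5%, the 9.5% splits in two. In 2qm = 3.5% of pairs the post-ICU death beats an ICU death. In 2q(1 − m − q) = 6.0% it faces a survivor, and the pair is decided on VFD60 or IL-6 instead of on death.

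**Shift in net benefit (wins minus losses) when total mortality is equal.** Let both arms have total mortality M, with ICU deaths m_t and m_c and post-ICU deaths q_t and q_c.
- Tier 1 contributes m_c(1 − m_t) − m_t(1 − m_c) = m_c − m_t = q_t − q_c.
- If post-ICU deaths have survivor-like VFD60, tier 2 adds nothing on average and the shift is q_t − q_c.
- If VFD60 = 0 for those deaths and survivors have more than 5 days, tier 2 adds (1 − M)(q_c − q_t). The total is then (q_t − q_c) × M.

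With M = 35%, ICU death 30% vs 35% and post-ICU death 5% vs 0%:
- survivor-like VFD60: 0.05
- VFD60 = 0: 0.05 − 0.05 × 0.65 = 0.0175 (0.0125 at M = 25%, 0.0225 at M = 45%)
- all deaths by day 60 in tier 1: 0.35 − 0.35 = 0

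**Simulation.** Finkelstein–Schoenfeld score test, 56 per arm, 2,000 trials per row. Survivors' VFD60 was normal with mean 35 and SD 15, limited to 0–60, and IL-6 AUC log-normal, both the same in each arm. Cells show net benefit and rejection rate.

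| ICU + post-ICU death, intervention vs control | ICU-only tier, survivor-like VFD60 | ICU-only tier, VFD60 = 0 | All deaths to day 60 in tier 1 |
|---|---|---|---|
| 35% + 5% vs 35% + 5% | 0.00; 4.9% | 0.00; 5.0% | 0.00; 5.6% |
| 25% + 10% vs 35% + 0% | 0.10; 16.4% | 0.04; 6.4% | 0.00; 5.8% |
| 25% + 5% vs 35% + 5% | 0.10; 14.6% | 0.11; 16.2% | 0.10; 15.2% |
| 25% + 0% vs 35% + 10% | 0.10; 15.8% | 0.18; 35.6% | 0.20; 44.6% |

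Monte Carlo error near 5% is about half a percentage point. Row 2 has equal total mortality and a 10-point shift: the ICU-only tier shows a benefit that is not there. Row 4 is the reverse: a true 20-point mortality difference is partly hidden.

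**The case against.** The best defence is that the sponsor chose a proximal outcome and named it accurately. The assigned ventilation protocol runs for at most 14 days, in-ICU death is close to it, and later deaths are reported as secondary endpoints. Weaning is standardised in both groups, and nothing in the article suggests that discharge will differ by arm. With identical splits the test keeps its level (row 1), and with equal post-ICU mortality the definition hardly matters (row 3). All of that stands. It limits the size of the problem but does not change the ranking of a ward death above every ICU death.

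A reader might infer four stronger things, and the article does not support them.
- *Post-ICU deaths are scored as survival throughout.* This is shown for tier 1 only. If Additional file 4 sets VFD60 to 0 for them, they lose to nearly every survivor in tier 2. The same file could also set a day limit for tier 1.
- *Ventilation after ICU discharge is counted as ventilator-free.* The phrase "and then on a daily basis up to 60 days or ICU discharge" schedules physiological variables and respiratory mechanics. It does not say that collection of VFD60 stops there.
- *A 5-point shift costs one sixth of the detectable effect.* Noether's formula with 112 patients gives (P − 0.5)² = (1.96 + 0.842)²/(3 × 112), so P = 0.653 and net benefit 2P − 1 = 0.306; 0.05/0.306 = 16%. That formula ignores ties and is not the trial's own assumption. The 0.05 also ignores the tier-2 offset: with VFD60 = 0 the ratio is 0.0175/0.306, about 6%.
- *Ward ventilation status could be added with one question at a planned follow-up contact.* The article describes no such contact.

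**Conclusion.** The point holds in this limited form. The article fixes a place-based top tier, with no day limit stated, above a 60-day tier. A patient who dies after ICU discharge and before day 60 therefore outranks every ICU death, and in an open-label trial discharge timing can influence which deaths count. A VFD60 = 0 rule in the unseen scoring file would shrink the distortion but not remove it.

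The size is conditional. For a 5-point difference between arms in the ICU/post-ICU split at equal total mortality of 35%, net benefit moves by about 0.02 to 0.05, depending on the VFD60 rule. There is no inflation of type I error when the split is the same. The article gives no evidence that the arms will differ in this way; the weakness is avoidable rather than a demonstrated bias. It should be corrected, but the trial remains analysable without the change.

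**What to change.** - Define tier 1 as all-cause death by day 60 from randomisation, wherever it occurs. The vital status needed for the 90-day mortality endpoint supplies this, provided the date of death is recorded.
- Set VFD60 to 0 for any death by day 60, after checking what Additional file 4 already says.
- Keep in-ICU mortality as a secondary endpoint. ICU deaths after day 60 would then leave tier 1 but still appear there, and in 90-day mortality if they occur by day 90.

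The cost is a change to the endpoint wording and the registry entry, and a rerun of the sample-size simulation if it used ICU death. Trial status reports that enrolment had not started at submission, so the change can be made without any outcome data.
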